# A randomised non-inferiority controlled trial of a single versus a four intradermal sterile water injection technique for relief of continuous lower back pain during labour

**DOI:** 10.1186/1471-2393-11-21

**Published:** 2011-03-23

## Abstract

**Background:**

Almost one third of women suffer continuous lower back pain during labour. Evidence from three systematic reviews demonstrates that sterile water injections (SWI) provide statistically and clinically significant pain relief in women experiencing continuous lower back pain during labour. The most effective technique to administer SWI is yet to be determined. Therefore, the aim of this study is to determine if the single injection SWI technique is no less effective than the routinely used four injection SWI method in reducing continuous lower back pain during labour.

**Methods/design:**

The trial protocol was developed in consultation with an interdisciplinary team of clinical researchers. We aim to recruit 319 women presenting at term, seeking analgesia for continuous severe lower back pain during labour. Participants will be recruited from two major maternity hospitals in Australia. Randomised participants are allocated to receive a four or single intradermal needle SWI technique. The primary outcome is the change in self-reported pain measured by visual analogue scale at baseline and thirty minutes post intervention. Secondary outcomes include VAS change scores at 10, 60, 90 and 120 min, analgesia use, mode of birth and maternal satisfaction.

**Statistical analysis:**

Sample size was calculated to achieve 90% power at an alpha of 0.025 to detect a non-inferiority margin of ≤ 1 cm on the VAS, using a one-sided, two-sample t-test. Baseline demographic and clinical characteristics will be analysed for comparability between groups. Differences in primary (VAS pain score) and secondary outcomes between groups will be analysed by intention to treat and per protocol analysis using Student's t-test and ANOVA.

**Conclusion:**

This study will determine if a single intradermal SWI technique is no less effective than the routinely used four injection technique for lower back pain during labour. The findings will allow midwives to offer women requesting SWI during labour an evidence-based alternative technique more easily administered by staff and accepted by labouring women.

**Trial Registration:**

ACTRN12609000964213

## Background

Almost one in three (30%) women in labour suffer from continuous lower back pain [1]. This pain is often associated with varying degrees of fetal malposition, particularly occipito-posterior position, which may apply pressure on pain-sensitive structures within the pelvis [2]. Characteristically, the pain persists throughout the normal painless resting intervals between contractions and is associated with greater analgesic requirement [2].

Administration of Sterile Water Injections (SWI) into the lower back is used in midwifery to provide pain relief to women experiencing lower back pain during labour. The sterile water causes osmotic and mechanical irritation resulting in a brief (15-30 second) and significant stinging sensation. The onset of pain relief follows almost immediately and may last for up to two hours. The procedure can be repeated a number of times [3]. The therapeutic effect has been explained by gate control theory [4] whereby the painful stinging stimulates competing nerve fibres, creating a block to the slower visceral signals from uterine contractions and back pain. The most frequently used SWI technique consists of four intradermal injections into the skin surrounding the Michaelis rhomboid over the sacral area.

Systematic reviews [3,5] and meta-analysis [6] have reported a significant reduction in self-reported pain measures in groups receiving SWI compared with controls. Authors concluded that SWI are an effective therapeutic intervention for the management of continuous back pain during labour. However, the included randomised controlled trials (RCT) were heterogeneous and incorporated different SWI techniques (single and four-injection SWI methods), methods of administration (intradermal or subcutaneous), and comparison groups (normal saline, transcutaneous electronic nerve stimulation and "standard care" defined as massage, counter pressure and water immersion). Authors of the systematic reviews [3,5] highlight that the analgesic efficacy obtained following administration of a single SWI at the most painful point [7] appear comparable to that obtained using the four injection SWI technique. The analgesic benefit of the single SWI method is further supported by results of a more recent randomised controlled trial (RCT) [8] which compared a single SWI to a placebo. The comparable analgesic benefit observed for both techniques has led authors to conclude there is need for further research [3,5]. There have been no trials conducted to date comparing the two SWI techniques.

There may be important clinical benefits in demonstrating the comparable analgesic efficacy of a single versus four needle SWI technique. The relative reduction in discomfort associated with the single injection procedure may increase the woman's satisfaction and acceptability with SWI treatment during labour, and willingness to use the procedure again in the future. In addition, improved resource allocation can be expected as only one midwife is required to administer a single SWI compared with the current recommendation for two midwives to administer the four injection technique. Therefore, the aim of this study is to compare a single intradermal SWI technique with the standard four injection intradermal technique in the degree and duration of analgesic benefit.

## Methods/design

A randomised, controlled, non-inferiority design was considered most appropriate method to answer our stated aim. Where two treatments, have both previously been shown to be superior to a placebo, and/or in cases where the use of a placebo may be unethical or impractical, a non inferiority design can be used to determine if one treatment is "no worse" than the other[9,10]. Usually, as in this study, the interventions include a new treatment and an active comparator, or a treatment currently in use. In relation to this trial, the single injection is the new treatment and the four injection technique is the active comparator. The null hypothesis is not proven if the measured effects of the two treatments lie within a specified non-inferiority margin [11].

### Hypothesis

The null hypothesis is conventionally stated in an RCT which assumes that there is no difference between the intervention group and controls. The null hypothesis places the onus on the intervention to be proven [12]. The null hypothesis is accepted if it cannot be refuted at the *a priori *defined level of significance. However, a non-inferiority design is attempting to show that two active treatments are similar in effect [13]. Therefore, the null hypothesis cannot be rejected if the measured treatment effects lie within a pre-specified non-inferiority margin [11]. Within non-inferiority design the sample size must be robust enough to test the quantitative or clinically relevant margin or definition of non-inferiority [13]. This margin is informed by considerations of clinically relevance, with any treatment differences falling outside this range indicating that any dissimilarity between treatments is unacceptably large [9].

The predefined non-inferiority margin for the present study was defined by the minimal clinically (i.e. not statistically) significant difference in the Visual Analogue Scale (VAS) to measure self-reported pain. Therefore, the null hypothesis (H_0_) would be "treatment is inferior", the alternative hypothesis (H_A_) "treatment is non-inferior":

H_0_: Difference between the four injection intradermal SWI and single injection intradermal SWI is ≥ 1 cm on the 10 cm VAS

H_A_: Difference between the four injection intradermal SWI and single injection intradermal SWI is < 1 cm on the 10 cm VAS

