### Sample size

A sample size of 133 in each group will be required to achieve 90% power to detect non-inferiority using a one-sided, two-sample t-test. The significance (alpha) of the test is 0.025. The non-inferiority margin is ≤ 1 cm on the VAS and the true difference between the means is assumed to be zero (cms). A standard deviation (SD) of ± 2.5 on the VAS was conservatively estimated from results reported in a recent meta-analysis [6] of SWI studies. As consent and randomisation will occur in the birth suite, attrition is expected to be minimal. However, we have estimated a 20% attrition to account for cases of precipitate birth prior to the assessment of the primary outcome, or other unforseen reasons for withdrawal such as emergency caesarean section. Thus a total of 319 participants will be required.

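### The Hypothesis section states the rejection rule in the wrong direction for its own null, and no section gives a decision rule that matches both that null and the one-sided alpha of 0.025

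*Protocol article*

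**What the plan says.** Four places in the protocol bear on how the primary conclusion is reached.

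- **Hypothesis, first paragraph.** After describing the conventional null of no difference, the text turns to non-inferiority designs and states: "Therefore, the null hypothesis cannot be rejected if the measured treatment effects lie within a pre-specified non-inferiority margin".
- **Hypothesis, second paragraph.** The trial's own null is inferiority. H0 reads "Difference between the four injection intradermal SWI and single injection intradermal SWI is ≥ 1 cm on the 10 cm VAS" and HA reads "Difference between the four injection intradermal SWI and single injection intradermal SWI is < 1 cm on the 10 cm VAS".
- **Methods/design, opening paragraph.** A related sentence reads: "The null hypothesis is not proven if the measured effects of the two treatments lie within a specified non-inferiority margin".
- **Statistical analysis.** The primary analysis is described as finding whether the treatment effect falls within ± 1 cm at a one-sided alpha of 0.025. The scenarios of Figure 4 are then explained: an interval lying inside the margin shows non-inferiority, and the error bars are 90% confidence intervals.

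The Sample size section fixes the intended operating characteristics: "A sample size of 133 in each group will be required to achieve 90% power to detect non-inferiority using a one-sided, two-sample t-test", and "The significance (alpha) of the test is 0.025".

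**The concern.** When H0 is inferiority, non-inferiority is concluded by rejecting H0, and what rejects it is evidence that the difference is below 1 cm. The Hypothesis sentence says that such results leave H0 standing. It would fit only a null of no difference, where failure to reject is read as similarity, and that is the inference a non-inferiority test is meant to avoid.

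The sentences in Hypothesis and Methods/design also compare the measured effects with the margin and mention no confidence limit. An observed difference inside the margin is not enough to reject H0 at 0.025.

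The Statistical analysis section puts the direction right, but its interval level belongs to a different alpha. At stake is the criterion for the trial's main conclusion: a reader who looks for it finds one reversed statement, one loose statement and one at the wrong level.

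**Working it through.** **Inputs (Sample size section).** Margin 1 cm, SD 2.5 cm, true difference 0, one-sided alpha 0.025, power 90%, 133 per arm.

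**Reproducing the plan's figure.** Normal approximation: n = 2 × (1.960 + 1.282)² × 2.5² / 1² ≈ 131.4, so 132 per arm. With the noncentral t distribution, power is 0.8993 at 132 and 0.9015 at 133. The stated 133 is therefore reproduced, and it presupposes the correct one-sided non-inferiority test at 0.025.

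**Standard error.** SE = 2.5 × √(2/133) = 0.3066 cm.

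**Orientation.** d is the true mean VAS decrease with four injections minus that with the single injection, so a positive d means the single injection is worse. The probabilities below use the normal approximation.

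**1. The Hypothesis sentence taken literally.** H0 cannot be rejected when the estimate is inside ± 1 cm. At d = 0, P(estimate outside ± 1) = 2 × Φ(−1/0.3066) = 2 × Φ(−3.26) ≈ 0.001. This is a ceiling on power: at most about 0.1%, against the stated 90%.

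**2. Direction corrected, but still judged on the point estimate.** Similarity is declared if the estimate is inside ± 1 cm.
- At d = 1: Φ(0) − Φ(−2/0.3066) = 0.50.
- At d = 1.2: Φ(−0.2/0.3066) = Φ(−0.65) ≈ 0.26.
- At d = 0: 0.999.

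**3. Confidence limit facing the margin.** Non-inferiority is concluded if the estimate plus z × SE is below 1 cm.

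| Rule | z | Estimate must be below | Error at d = 1 | Power at d = 0 |
|---|---|---|---|---|
| Upper 90% limit < 1 cm | 1.645 | 1 − 1.645 × 0.3066 = 0.50 cm | 0.05 | 0.947 |
| Upper 95% limit < 1 cm | 1.960 | 1 − 1.960 × 0.3066 = 0.40 cm | 0.025 | 0.904 (0.9015 by noncentral t) |

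Only the last row has the error rate and power on which the sample size is based. The 90% and 95% rules disagree when the observed deficit lies between about 0.40 and 0.50 cm.

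**The case against.** The best defence is that the faulty sentence is not the operative rule. It sits in a general, referenced paragraph about non-inferiority designs, and the trial-specific paragraph that follows gives H0 and HA in the right direction. The Sample size section names a one-sided t-test at 0.025, and the Statistical analysis section concludes non-inferiority from an interval inside the margin. An analyst would probably follow those. This stands as a limit on the consequence. It does not clear the point, because the sentence is offered as the non-inferiority rule and the section that could override it uses an interval level that implies one-sided 0.05.

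Four stronger readings are tempting, and the protocol does not support them:

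- **That the trial as planned cannot establish non-inferiority at its alpha.** The test, the alpha and the direction of the interval rule are stated correctly outside the Hypothesis sentence.
- **That the literal rule rejects H0 half the time at a true 1 cm deficit.** This needs the converse, that results outside the margin do reject H0, which the text never states. Only the 0.1% power ceiling follows from the sentence itself.
- **That the Methods/design sentence is reversed too.** For a null of inferiority, calling it not proven inside the margin is loosely the right way round. Its fault is the reference to measured effects.
- **That the remark about accepting an unrefuted null must go.** It describes conventional trials and is closed off before the text turns to non-inferiority.

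The 50% and 26% figures also depend on reading the measured effect as a bare point estimate. The wording allows that reading, but other sections attach a test and an interval.

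**Conclusion.** The point holds in limited form. The Hypothesis section contradicts its own H0 on the direction of rejection, and both it and Methods/design refer to the measured effect where a confidence limit is needed. The Statistical analysis section corrects the direction but pairs 90% intervals with a one-sided alpha of 0.025, so no section writes out a rule that fits both H0 and alpha.

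The practical size lies mainly in the interval level: 5% error instead of 2.5%, and an observed-deficit threshold of about 0.50 cm instead of 0.40 cm. A point-estimate reading would be far worse (50% error at the margin), but it is a possible reading and not the evident plan. All figures assume 133 analysed per arm and SD 2.5 cm, as planned. The sample size, H0 and HA are unaffected. This should be corrected, but it does not undermine the design.

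**What to change.** Replace the Hypothesis sentence, and tidy the similar one in Methods/design, with a single rule:

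> H0 is rejected, and non-inferiority concluded, only if the upper limit of the two-sided 95% CI for the difference in mean VAS decrease at 30 minutes (four injections minus single) is below 1 cm; otherwise non-inferiority is not shown.

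In the Statistical analysis section and Figure 4, change the interval level from 90% to 95%. The scenarios there are described with inferiority to the left of zero, which is the opposite sign. State the sign convention once, so that the limit facing the margin is unambiguous.

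The cost is a few sentences and a redrawn figure. Nothing changes in the data, conduct or sample size, or in the stated H0 and HA.

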### Study site and population

The study population will be recruited from the Birth Suites of two major maternity hospitals. Women eligible for the study are those that request analgesia for continuous severe lower back pain during labour (≥7 on the VAS) and provide informed consent. The categorisation of severe back pain as ≥7 on the VAS has been previously validated [14] and consistent with defined inclusion criteria in previous SWI studies [14-17]. Women with a baseline VAS score of <7 were more likely to find administration of the procedure unacceptable [16].

The eligibility criteria are pre-specified as:

### Inclusion criteria

Participants eligible for the study will be defined as:

Women at term (between 37 and 42 weeks)

Nulliparous or multiparous

Singleton pregnancy

Cephalic presentation

First stage labour (spontaneous or induced)

No previous analgesia pharmacological analgesia (nitrous oxide inhalation, narcotics)

Back pain assessed by VAS as ≥7

Ability to give informed consent. This may exclude women of non-English speaking backgrounds, where an interpreter is unavailable, and those women whose consent is required to be provided by a parent or guardian.

### Exclusion criteria

Gestation <37 weeks

Multiple pregnancy

Malpresentation (Breech Transverse etc.)

Second stage labour

Pharmacological analgesia prior to SWI

Back pain assessed by VAS <7

Women whose labour would be considered high risk.

### Interventions

#### Control group

Participants randomised to the control group will be given SWI using the standard four injection intradermal technique into the skin surrounding the Michaelis rhomboid over the sacral area. Anatomically, the injections will be administered: two over each posterior superior iliac spine (PSIS) and two three cm below and one cm medial to the PSIS (Figure 1). Minor discrepancies or changes to the anatomical position or alignment of the four injections have not been shown to impact on any analgesic effect [18].

**Figure 1 F1:**
[figure not shown]
**The four injection technique**.

#### Intervention group

Participants randomised to the intervention group will be given SWI using the single injection intradermal technique.

The anatomical site for the single injection will be over the single most painful point as indicated by the woman (Figure 2).

**Figure 2 F2:**
[figure not shown]
**The single injection technique**. Woman indicates the most painful point or central to the most painful area.

#### Primary outcome

Decrease in pain measured by VAS at 30 minutes post-intervention.

#### Secondary outcomes

Secondary outcomes will include:

a) Pain score measured by VAS 10, 60, 90 and 120 mins post-intervention

b) Level of administration discomfort associated with SWI procedure (measured by VAS at 10 minutes post SWI)

c) Subsequent analgesia use (pharmacological and non-pharmacological)

d) Mode of birth

e) Likelihood to use again with subsequent labour

f) Patient satisfaction with analgesic effect

### Sample size

A sample size of 133 in each group will be required to achieve 90% power to detect non-inferiority using a one-sided, two-sample t-test. The significance (alpha) of the test is 0.025. The non-inferiority margin is ≤ 1 cm on the VAS and the true difference between the means is assumed to be zero (cms). A standard deviation (SD) of ± 2.5 on the VAS was conservatively estimated from results reported in a recent meta-analysis [6] of SWI studies. As consent and randomisation will occur in the birth suite, attrition is expected to be minimal. However, we have estimated a 20% attrition to account for cases of precipitate birth prior to the assessment of the primary outcome, or other unforseen reasons for withdrawal such as emergency caesarean section. Thus a total of 319 participants will be required.

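### The 20% attrition allowance is multiplied on (266 × 1.20) instead of divided out (266 / 0.80), so 319 women do not leave 133 per group after a 20% loss

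*Protocol article*

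**What the plan says.** All the inputs are in the Sample size section of the protocol article. It states: "A sample size of 133 in each group will be required to achieve 90% power to detect non-inferiority", "using a one-sided, two-sample t-test", with a one-sided alpha of 0.025, a margin of 1 cm on the VAS, an SD of 2.5 and a true difference of zero.

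The section then says that attrition is expected to be minimal, but adds an allowance: "we have estimated a 20% attrition". The reasons given are precipitate birth before the primary outcome is assessed and other withdrawals such as emergency caesarean section. It ends: "Thus a total of 319 participants will be required".

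The Methods/design part of the Abstract repeats the number as the recruitment target: "We aim to recruit 319 women presenting at term".

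The Statistical analysis section uses the same 20% as a dropout rate. If dropout exceeds that allowed margin, a per-protocol analysis is run in addition to the intention-to-treat analysis.

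**The concern.** An attrition rate is a proportion of the women randomised. To keep a given number evaluable, that number has to be divided by one minus the rate. The stated total matches the other operation, in which 20% of the evaluable number is added on top. If so, the required group size, the attrition rate and the total in one paragraph contradict each other, and the trial falls below its stated 90% power at exactly the attrition it claims to have covered.

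The 20% figure is used again in the Statistical analysis section as the loss the design allows. Between the loss that 319 really covers and 20%, the trial would be below its required number while the plan still counted the loss as provided for.

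**Working it through.** **Inputs (Sample size section):** one-sided alpha 0.025; margin 1 cm; SD 2.5 cm; true difference 0; equal groups; 133 per group; attrition 20%; total 319.

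**1. The group size reproduces.** Power for the one-sided two-sample t-test comes from the noncentral t distribution with n₁ + n₂ − 2 degrees of freedom and noncentrality

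δ = margin / (SD × √(1/n₁ + 1/n₂)).

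- 132 per group: δ = 1 / (2.5 × √(2/132)) = 3.250; power 0.8993.
- 133 per group: δ = 1 / (2.5 × √(2/133)) = 3.262; power 0.9015.

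So 133 is the smallest group size that reaches 90%, and it has no slack to absorb a shortfall. The evaluable total is 2 × 133 = 266.

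**2. The total reproduces only by multiplication.**

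- 266 × 1.20 = 319.2, which gives 319 when rounded down.
- 266 / (1 − 0.20) = 332.5, which gives 333, or 2 × 167 = 334 for equal groups.

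Starting from the normal-approximation size of 132 per group does not rescue the figure: 264 / 0.80 = 330.

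**3. What 319 leaves after a 20% loss.**

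- 319 × 0.80 = 255.2 women, about 127.6 per group. That is 5 to 6 per group below 133, and 266 − 255 = 11 in total.
- With 128 and 127 women: δ = 1 / (2.5 × √(1/128 + 1/127)) = 3.194; power 0.889. The normal approximation gives 0.892.

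**4. The attrition that 319 does cover.** 1 − 266/319 = 0.166, so 266 women remain only up to 16.6% attrition.

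**5. Check of the divided-out total.** 334 × 0.80 = 267.2, or 133.6 per group; power 0.903.

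| Randomised | Attrition | Evaluable | Power |
|---|---|---|---|
| 319 | 5% | 303 | 93.5% |
| 319 | 10% | 287 | 92.2% |
| 319 | 15% | 271 | 90.7% |
| 319 | 16.6% | 266 | 90.1% |
| 319 | 20% | 255 | 88.9% |
| 334 | 20% | 267 | 90.3% |

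The shortfall in the randomised total is 333 − 319 = 14 women (14/333 = 4.2%), or 334 − 319 = 15 with equal arms (15/334 = 4.5%).

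**The case against.** The arithmetic is hard to dispute; its importance can be disputed.

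- **Size.** The loss is about one percentage point of power. Type I error, the margin and the validity of the non-inferiority test are untouched. The SD is described as a conservative estimate, and with 255 women power is back at 90% if the true SD is 2.45 instead of 2.5. All of this stands, and it limits the weight of the point.
- **Likelihood.** The plan expects minimal attrition, since women are randomised in the birth suite and the primary outcome follows at 30 minutes. At 15% loss or less, 319 gives more than 90% power. This also stands. But the paragraph offers 20% as the loss that has been allowed for, and that statement is not met.
- **A different reading of 20%.** The figure could be meant as 20% added on top. The text does not support this: the Sample size section describes women lost before the primary outcome, and the Statistical analysis section calls the same figure a dropout rate.
- **Intention to treat.** The Statistical analysis section keeps women who give birth or choose narcotic or regional analgesia before the 30-minute score in the intention-to-treat analysis, so 255 may look like a worst case. However, the Sample size section itself counts precipitate birth before the primary outcome as attrition, and a woman with no 30-minute score adds no measured outcome. The count of 255 is the one the plan's own allowance implies.
- **Per-protocol trigger.** The 20% rule operates in the same way whether the total is 319 or 334. That is true. Its relevance here is only that it shows 20% being treated as a covered loss.

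**Conclusion.** The concern holds. The total of 319 is 266 × 1.20 and does not deliver 133 per group, or 90% power, at the stated 20% attrition. At that loss about 255 women remain and power is 88.9%, against 90.1% at 133 per group. The total covers attrition up to 16.6%. Keeping 266 after a 20% loss takes 333 women, or 334 in equal arms.

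The power figures rest on the plan's own assumptions (SD 2.5, true difference 0, margin 1 cm, one-sided alpha 0.025), with losses spread evenly over the groups and lost women contributing no 30-minute score. This is a misstated figure with a small consequence. It does not make the trial unsound, but it should be corrected.

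**What to change.** Either of two changes makes the paragraph true.

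1. **Keep 319 and restate what it delivers (preferred).** Suggested wording for the Sample size section: *A total of 319 participants allows for 16.6% attrition at 90% power; at 20% attrition (255 women) power is 88.9%.* The Abstract's target then stays as it is. In the Statistical analysis section, the 20% per-protocol threshold should no longer be described as the margin the sample size allows for. The cost is a slightly less favourable figure and no extra participants.
2. **Keep the 20% allowance and correct the total.** Change 319 to 334 in the Sample size section and in the Methods/design part of the Abstract. The cost is 15 more women.
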